### Interventions

The parent training program includes the behavioral techniques that were identified as effective for reducing behavioral difficulties (i.e., oppositional, defiant, aggressive, hyperactive, impulsive, and inattentive behavior) in a preceding microtrial [33] and in the broader literature [22, 23, 31, 32, 34]. Importantly, all behavioral techniques are explained to parents and based on a functional analysis, the most suitable techniques are selected and tailored to the specific problem behaviors that parents experience with their child and to the home context. Prior to the brief training, with a researcher parents choose four daily occurring target behaviors from the list of target behaviors (see Primary Outcome) that they prefer to work on in the training [33, 36, 37]. For each of the four behaviors, parents also indicate in which situation the behavior occurs, using the situations that are included in the Home Situation Questionnaire [37]. The therapist providing the brief training receives a list of the chosen four behaviors in specific situations before the training.

In the first session, parents are briefly educated about supposed underlying mechanisms of behavioral difficulties in children. They learn that children with behavioral difficulties may have problems in executive functioning, such as inhibition or working memory, which may influence the way they process environmental information and exert control over their behavior [38, 39]. Parents are taught how they can use antecedent techniques (i.e., setting rules, giving clear instructions, structuring situations, discussing situations in advance) to support their child’s executive functioning and elicit more desirable and prosocial behaviors. Parents are also taught that children with behavioral difficulties may show altered sensitivity to reinforcement and punishment, which may influence how children learn from rewards and negative consequences and the way in which their behavior is shaped by environmental consequences as provided by parents [40–44]. Their altered reinforcement sensitivity may lower the likelihood that children change behavior in response to corrective reactions and result in behaviors that are reward-oriented on the short term [40, 43]. The therapist explains that consequent techniques (i.e., reinforcement [e.g., praise], planned ignoring, non-violent discipline techniques [e.g., correction, natural consequences]) are important to deal with these sensitivities, while emphasizing that the majority of the used consequent techniques should concern reinforcement. In their explanations, therapists also stress parents that the psycho-education is based on research involving many children and could therefore not directly apply to the situation of their child. After this psycho-education, the parents and therapist select a first target problem behavior along with the specific situation in which this behavior occurs daily. This behavior is chosen from the four behaviors in specific situations that parents selected beforehand with a researcher to target in the training. Together, the parents and therapist make a functional analysis of the selected behavior and create an individually tailored intervention plan. This plan contains the most suitable of the four antecedent techniques and one consequent technique (i.e., praise). The techniques are selected according to the functional analysis and adapted to the abilities and needs of the child and parents. Parents write down their intervention plan with the therapist and receive a handout with explanations of the techniques. Directly after each session, parents carry out their intervention plan at home the next week.

In the second session, the first plan is evaluated and adapted if necessary. The parents and therapist briefly recapitulate the psycho-education and intervention plan of the first session and discuss a second target problem behavior in the same way as the first problem behavior. They make an individually tailored intervention plan for the second target behavior, which again includes the most suitable techniques of all discussed antecedent and consequent techniques, based on the functional analysis of the second target behavior. Based on the results of our microtrial that antecedent techniques are effective sooner after the training (i.e., immediately) and are more effective in decreasing symptoms of inattention than consequent techniques [33], the intervention plan of the first session mainly contains antecedent techniques, while the intervention plan of the second session includes both antecedent and consequent techniques. The consequent techniques always include forms of reinforcement (e.g., praise, rewards) and can optionally include ignoring or mild negative consequences. In the third session, the second intervention plan is evaluated and adapted if necessary. Maintenance training is provided by encouraging parents to think about how the techniques can be used for other problems. Furthermore, during this session parents rehearse and practice designing an intervention plan accordingly for possible new behavior problems.

In the optional booster sessions, parents can discuss either the same or new target behaviors and create or adapt an intervention plan with the antecedent and consequent techniques that are taught in the earlier sessions. Parents are stimulated by the therapist to use the steps they have learned in the earlier sessions. Parents implement new or adapted intervention plans directly after the session. Booster sessions are not meant as prolongation of the brief training, but as stand-alone sessions to support parents in refreshing and maintaining to apply the learned techniques. Booster sessions can be combined with any CAU.

Parents in the control arm receive CAU, which in Dutch mental healthcare typically consists of psychoeducation, parent counseling and support, medication, longer behavioral parent training programs, family therapy, support at school, and/or cognitive behavior therapy or other therapy or support for the child.

### Treatment fidelity

Intervention fidelity (i.e., the percentage of items covered in each session) is assessed with a fidelity checklist using an adapted version of the procedures of Abikoff and colleagues [45, 46]. This implies that all intervention sessions (including the booster sessions) are audiotaped. The audiotapes of 20% randomly selected sessions will be scored on intervention fidelity by independent evaluators. After each session, therapists also have to complete a fidelity checklist in which they are asked which items they covered.

### Recruitment

Parents of children with behavioral difficulties who are referred to one of the participating Dutch mental healthcare centers are recruited by clinicians within these centers. After the diagnostic assessment of the child and before any treatment has started, the clinicians involved in the diagnostic assessments inform parents of children who seem eligible about the study and hand out an information letter. Clinicians provide researchers with contact information of parents that have consented to sharing information and are interested in participation. The researchers then further inform parents about the trial through telephone contact. If parents want to participate, the researchers ask both parents, or other legal caretakers of the child, to provide informed consent. By default, parents have 14 days to decide upon participation and ask the researchers any questions. If needed, parents can ask for more time to decide upon participation. Once parents have provided consent, the researchers screen whether families are eligible for the study and inform parents whether they can participate.

### Allocation to study arms

Randomization is performed with an online generated randomization schedule [47], using blocks of six participants for each healthcare center to ensure equal allocations to both arms within and across centers. The randomization schedule is only known and administered by independent researchers who are not involved in the trial in any other way. When participants can be randomized, the independent researchers are informed at which healthcare center the parents are participating and asked to inform the responsible researchers about which condition has been randomly assigned to these parents. Randomization occurs directly after the baseline measurement (T0).

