## Methods

### Study design

In this two-arm multi-center randomized controlled trial, parents of children who experience behavioral difficulties in the home setting and were referred to a child mental healthcare center, are randomly assigned (1:1 ratio) to either (a) three sessions of brief behavioral parent training with optional booster sessions, or (b) CAU, as regularly provided by the involved mental healthcare centers. There are no restrictions regarding the type (e.g., psychoeducation, parent counseling and support, individual child therapy, medication) or duration of CAU, only the brief parent training investigated in this trial is not allowed. Both parents and children in the brief behavioral parent training group are not allowed to receive CAU until the first posttreatment assessment (T1). After that, CAU is allowed and parents can also make use of booster sessions with the therapist who provided the training.

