### Eligibility criteria

Families eligible for the trial must meet the following inclusion criteria:The child is aged between 2 and 12 years;Parents have to identify at least four behavioral difficulties of the child that occur in the home setting and that they want to target in the training, using an adapted version of a list of target behaviors [33, 36]. This list contains 29 behaviors that can be targeted in the training, such as hyperactive, impulsive, inattentive, oppositional and defiant behavior. The items are derived from target problems that parents mentioned in previous behavioral parent training groups and concern child behaviors that are commonly targeted in behavioral parent training in clinical practice, confirming ecological validity [36].

Exclusion criteria are:The child uses psychotropic medication (currently or in the month before the screening);The child has at any time received a diagnosis of autism spectrum disorder (ASD) in clinical practice, as (parents of) children with ASD may have different needs and therefore may require different treatments than children with behavioral difficulties without ASD;The child has a known IQ-score below 70, as (parents of) children with intellectual disabilities may have different needs and therefore may require different treatments than children with behavioral difficulties and typical intellectual abilities;Parents received behavioral parent training aimed at reducing the behavioral difficulties of the concerned child in the year prior to the start of the study;It is not a suitable period for the parents and/or the child to participate in the study (e.g., moving, divorce);The child is not living in the same household as the parent(s) who participate(s) in the trial during at least four weekdays (to ensure that our primary outcome can be reported by the same informant(s) and that parents can apply the intervention plans at home).

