## Discussion

This study protocol describes a multi-center randomized controlled trial investigating the short- and longer-term effectiveness and the cost-effectiveness of a brief, individually tailored behavioral parent training program that aims to reduce children’s behavioral difficulties. Although behavioral parent training is an evidence-based psychosocial treatment for reducing children’s behavioral difficulties, few families currently receive the intervention. This may be due to, among other reasons, a shortage of certified therapists, long waiting lists, and a perceived rigidity and length of behavioral parent training programs. Brief and individually tailored parenting interventions may reduce these problems and could therefore be a promising way to make behavioral parent training more accessible for parents.

We anticipate multiple challenges that the trial could face. For instance, clinicians’ policies and attitudes towards parent training may complicate the enrollment of eligible families in clinical practice [26]. Clinicians might be used to their work routines and experience resistance or difficulty getting acquainted with the trial, for instance because they do not feel sufficiently knowledgeable about the contents and effects of the brief behavioral parent training or feel uncertain about the procedures and administration that come with families’ participation in the trial, or because families may express hesitation about participating in a trial. As a result, clinicians may not refer eligible families or (intuitively) recommend usual care (e.g., other parent training programs or parent support, child treatments, medication) rather than the trial. We aim to tackle this hindrance by making clinicians aware that participation in this trial is in line with the stepped-care approach as delineated in international and Dutch treatment guidelines for children with ADHD and for children with disruptive behavior disorders, which suggest offering non-pharmacological treatment that includes psycho-education and practical advices, such as the brief behavioral parent training, before starting more intensive treatment or medication [6, 8, 10, 12].

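### A single, published block size of six per centre lets the research team deduce up to a quarter of allocations in advance; varying and withholding the size is a cheap improvement

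*Protocol article*

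**What the plan says.** All references are to the Protocol article.

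- **Block size.** Allocation to study arms sets the schedule "using blocks of six participants for each healthcare center", with the aim "to ensure equal allocations to both arms within and across centers". Study design gives a 1:1 ratio, so each block holds three families per arm. No variation in block size is described.
- **Who holds the list.** "The randomization schedule is only known and administered by independent researchers who are not involved in the trial in any other way".
- **Who learns the result.** The same section has these independent researchers told the family's centre and then asked to "inform the responsible researchers about which condition has been randomly assigned to these parents".
- **Timing.** Randomization follows consent, eligibility screening and the baseline measurement (T0).
- **Who decides on entry.** Under Recruitment, "the clinicians involved in the diagnostic assessments inform parents of children who seem eligible about the study". The researchers then telephone families, obtain consent and screen. One exclusion under Eligibility criteria is a matter of judgement: "It is not a suitable period for the parents and/or the child to participate in the study".
- **Masking.** Only the coding of the mealtime recordings is described as masked (Observed parent and child behaviors). Three training sessions against care as usual cannot be hidden from those who arrange them.

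**The concern.** Keeping the list with outsiders protects it from being read, but not from being worked out. When every block has the same known size and each allocation is disclosed with its centre, a tally per centre shows when one arm of the current block is used up. The remaining places in that block are then known.

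This matters only if someone with that knowledge still has a decision to make. The research team has two: whether a family passes screening, including the judgement on a suitable period, and which of several ready families is put forward first. If either decision leaned on the coming arm, the arms could differ at entry in severity or motivation. The primary outcome is rated by parents who know their arm, and the planned effect is small (d = 0.25, Sample size calculation), so even a modest difference at entry could be material.

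**Working it through.** The article gives no predictability figure, so there is none to reproduce. The inputs are block size 6 (Allocation to study arms), ratio 1:1 (Study design) and 93 families (Sample size calculation). The number of centres and the rate of accrual are not given and are varied below as assumptions.

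**1. Certain allocations in a complete block.** There are C(6,3) = 20 equally likely orders. An allocation is certain once one arm has had its three places.

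| Position in block | 1 | 2 | 3 | 4 | 5 | 6 |
|---|---|---|---|---|---|---|
| Chance it is certain | 0 | 0 | 0 | 0.10 | 0.40 | 1.00 |

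The sum is 0.10 + 0.40 + 1.00 = 1.5 per block. The closed form for a block of 2m agrees: 2m/(m+1) = 6/4 = 1.5 with m = 3. The share is 1.5/6 = 25%. Of the 20 orders, 12 have one certain place, 6 have two and 2 have three: (12×1 + 6×2 + 2×3)/20 = 30/20 = 1.5.

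**2. Best guess.** Always guessing the arm that is behind in the current block is right 68.3% of the time, against 50% by chance.

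**3. Incomplete last blocks.** Summing the position-wise chances over 93 families spread evenly over the centres:

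| Centres (assumed) | Expected certain allocations | Share of 93 |
|---|---|---|
| 1, 3 or 5 | 22.5 | 24.2% |
| 6 | 18.3 | 19.7% |
| 10 | 15.3 | 16.5% |

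The share does not fall steadily with the number of centres, because it depends on where the last block stops. It drops below 10% from about 19 centres.

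**4. Other families waiting ahead.** If k families at the centre are ahead in the queue and not yet allocated, the arm of the family under consideration must be predicted without their results. A place is then certain only if one arm was already used up k places earlier.

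| Waiting ahead (assumed) | Certain share | Best guess correct |
|---|---|---|
| 0 | 1.5/6 = 25% | 68% |
| 1 | (0.10 + 0.40)/6 = 8.3% | 60% |
| 2 | 0.10/6 = 1.7% | 57% |

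**5. Effect of varying the size.** Simulation of an observer who sees every allocation and even knows the set of possible sizes, but not their order:

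| Sizes in random order | Certain share | Best guess correct |
|---|---|---|
| 6 only | 25% | 68% |
| 4, 6, 8 | about 2% | about 67% |
| 6, 8, 10 | about 2% | about 65% |

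**The case against.** The best defence is that discretion and prediction fall at different times. Between referral and allocation come a default 14 days to decide (extendable), consent, screening, and a baseline with at least four weekdays of telephone ratings. By the time of allocation the family is already consented, found eligible and measured. Whoever screens must predict a later slot, and step 4 of the working shows how quickly certainty is lost once other families are in the queue. This stands, and it is why 25% is a ceiling. It does not remove the point: with no family waiting at a centre the full figure applies, and the order of families who become ready together stays open to influence.

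Two stronger readings are tempting, and the article supports neither.

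- **That referring clinicians can foresee the arm.** Allocations are reported to the responsible researchers. Nothing shows that a diagnosing clinician sees a centre's whole sequence.
- **That the article itself predicts selection by arm.** The Discussion warns that "clinicians may not refer eligible families or (intuitively) recommend usual care", but the alternative it has in mind is the trial as a whole. It attributes this to routines and unfamiliarity and offers a countermeasure. It describes a barrier to recruitment before enrolment, which does not depend on the coming arm.

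It is also an inference that the individuals who receive allocations are those who screen, since the article speaks only of researchers in both places. Finally, baseline severity is measured before allocation, so an imbalance on it would be visible; motivation would be harder to see.

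**Conclusion.** The point holds as a minor improvement, not as an error or contradiction in the plan. Stratified blocks held by independent staff and opened after baseline are a defensible scheme; the weakness is the single, printed size.

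Up to 25% of allocations can be deduced in advance, with a best guess right 68% of the time. This rests on complete blocks, full knowledge of the centre's history and an empty queue. Under the assumptions shown, the certain share is about 16% to 24% for 1 to 10 centres, about 8% with one family waiting and under 2% with two. That the trial is open is inferred from the nature of the arms. A reader might infer that selection has taken place; the article offers no evidence of that, only of an opportunity, and mainly for the research team.

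**What to change.** For blocks not yet opened, have the same independent researchers regenerate the schedule within each centre with randomly varied block sizes, for example 4, 6 and 8. Keep the sizes from the research team and the centres until recruitment ends. Stratification by centre is unchanged.

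The gain is specific. Certain allocations fall from 25% to about 2%, but the best guess falls only from 68% to about 67%, so the change removes near-certain prediction and leaves the general drift towards the arm that is behind.

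The cost is one new list and slightly looser balance. An unfinished block of six can leave a centre up to three families apart, one of eight up to four and one of ten up to five, hence one or two more families per centre. The reach is also limited: the article expects inclusion to finish around the beginning of 2025, so only blocks still unopened would benefit.

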### Procedure

Parents in the brief behavioral parent training arm receive three sessions of behavioral parent training. The first two sessions take 120 min each and are planned one or two weeks apart. The third session takes 60 min and is planned one week after the second session. To take parents’ and therapists’ availability into account, some flexibility in planning is allowed as long as all three sessions are planned within six weeks with at least one week between two consecutive sessions. After the third session, parents wishing to receive additional support can receive CAU and/or booster sessions. The booster sessions take 60 min each and can be provided maximally once every four weeks up to one year after the last session of the brief behavioral parent training program. Booster sessions can be suggested by the therapist who provided the brief behavioral parent training or by other involved clinicians, or requested by parents themselves.

The trial contains four measurement occasions, see Fig. 1 for the participant timeline. T0 takes place after parents provide consent and are found eligible for participation, before randomization. The first posttreatment measurement (T1) takes place one week after the third session for parents in the brief behavioral parent training arm and eight weeks after T0 for parents in the CAU arm. The second posttreatment measurement (T2) takes place six months after T1 and the third posttreatment measurement (T3) takes place twelve months after T1. Participation in the trial therefore takes approximately 14 months in total. The care families receive at the child mental healthcare center may terminate sooner if they do not need or want care anymore.

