**Methods:**

Parents of children aged 2–12 years referred to a child mental healthcare center are randomized to (i) three sessions of behavioral parent training with optional booster sessions or (ii) care as usual. To evaluate effectiveness, our primary outcome is the mean severity of five daily ratings by parents of four selected behavioral difficulties. Secondary outcomes include measures of parent and child behavior, well-being, and parent–child interaction. We explore whether child and parent characteristics moderate intervention effects. To evaluate cost-effectiveness, the use and costs of mental healthcare and utilities are measured. Finally, parents’ and therapists’ satisfaction with the brief program are explored. Measurements take place at baseline (T0), one week after the brief parent training, or eight weeks after baseline (in case of care as usual) (T1), and six months (T2) and twelve months (T3) after T1.

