To address this need, this randomized controlled trial evaluates the effectiveness of a brief and individually tailored behavioral parent training program with optional booster sessions for children with behavioral difficulties. The program is based on intervention elements that were effective in reducing children’s behavioral difficulties in the broader literature and our earlier work: antecedent techniques (i.e., stimulus control techniques) and consequent techniques (i.e., contingency management techniques) [22, 31, 32]. Antecedent techniques are aimed at changing child behavior by manipulating the antecedents of this behavior (e.g., by setting clear rules and providing structure) and consequent behavioral techniques are aimed at changing child behavior by manipulating their consequences (e.g., by praising desired behavior and ignoring undesired behavior). In a recent microtrial in which we evaluated the efficacy of antecedent and consequent techniques, both sets of techniques were found to reduce behavioral problems of children with ADHD in brief (i.e., two sessions) behavioral parent training, of which antecedent techniques were especially effective in decreasing inattention [33]. This microtrial also showed that the magnitude of effects of a brief program (i.e., medium-sized effects) was similar to those of traditional, longer programs on reducing child behavioral difficulties [23, 33, 34].

Building upon the findings of our microtrial, the brief behavioral parent training of the present trial consists of two sessions in which antecedent and consequent techniques are combined and a third session aimed at the evaluation and maintenance of applying the learned techniques. To prevent relapse and the possible use of other, more intensive and expensive treatments, parents can receive booster sessions in the first year after the brief training. Similar to the microtrial, the behavioral parent training is individually tailored by letting parents select four target behaviors they want to address in the training and by creating an individually tailored intervention plan based on the functional analysis (see [33]). A non-randomized pilot study (*N* = 28) preceding the present trial indicated a relatively low dropout rate (14.2%), high treatment feasibility and parent and clinician satisfaction, and a reduction of children’s behavioral difficulties from pre to post intervention [35].

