### Statistical analysis

Data will be analyzed on an intention-to-treat basis. To examine the effects of the intervention on the primary and secondary outcomes, we will conduct multilevel analyses (mixed modeling), taking missing data into account [75]. Depending on the fit of the models, up to four hierarchical levels will be distinguished: outcomes (level 1), nested within children (level 2), nested within therapists (level 3), nested within healthcare centers (level 4). Random intercepts at the subject level, therapist level and healthcare center level will be included only if the Likelihood Ratio Test shows a significant improvement of the model fit. Time will be included as short-term (T1) and longer-term (T2, T3) within-subjects factors and condition (brief parent training vs. CAU) as between-subjects factor. The interaction between time and condition will be examined to interpret changes over time between conditions. To examine whether the candidate moderator variables moderate the intervention effects, these variables will also be added as interaction effects to the multilevel analyses.

To assess the cost-effectiveness of the brief behavioral parent training compared to CAU, we will calculate the Incremental Cost Effectiveness Ratio (ICER) from a societal perspective. We will perform both a cost-utility analysis (based on QALYs) and cost-effectiveness analyses (based on the daily ratings of behavioral difficulties and based on ECBI-I scores). An ICER is calculated by dividing the difference in the total costs by the difference in the total effect (either QALYs or the daily ratings of behavioral difficulties and ECBI-I scores, respectively). In these analyses, the costs of healthcare will be used and interpolated to the previous 12 months. We will compare each ICER based on relevant willingness to pay thresholds. Bootstrapping will be used to calculate the reliability of our estimates.

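### Training-arm families who never reach the third session have no defined T1, T2 or T3 date, so their outcomes may go missing in one arm of an intention-to-treat comparison

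*Protocol article*

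**What the plan says.** The Procedure section of the protocol article gives one T1 rule per arm. For the training arm: "The first posttreatment measurement (T1) takes place one week after the third session for parents in the brief behavioral parent training arm". For the control arm: "eight weeks after T0 for parents in the CAU arm". The later visits inherit whichever anchor applies: "The second posttreatment measurement (T2) takes place six months after T1 and the third posttreatment measurement (T3) takes place twelve months after T1". The Methods paragraph of the abstract is looser about the training arm: "one week after the brief parent training, or eight weeks after baseline (in case of care as usual) (T1").

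Allocation to study arms places randomisation directly after T0, before any session. Statistical analysis states: "Data will be analyzed on an intention-to-treat basis", using mixed models that take missing data into account.

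A care rule is tied to the same visit. Study design says: "Both parents and children in the brief behavioral parent training group are not allowed to receive CAU until the first posttreatment assessment (T1"). Procedure instead opens CAU and booster sessions to training-arm families once the third session has taken place.

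Several other measures also need these dates. Adverse reactions are asked only at T3. The EQ-5D and the care-use questionnaire are taken at T0 and T3. The inventory from patient records runs from T0 to T3. Satisfaction with the training is asked at T1.

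**The concern.** The third session is an event that only families who complete the training reach. Eight weeks after T0 is a date that every family reaches. Families are randomised before any session, so some will be in the training arm without ever having a third session. The written rule gives them no T1, and hence no T2 or T3.

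If they are not measured, they contribute at most their T0 data, and the mixed model in effect fills in their later outcomes from training-arm families who did complete. That is safe only if stopping is unrelated to later outcome, given what was observed. It is not safe if families stop because the training does not help or suit them. A CAU family that stops or never starts care keeps its assessment date, so this route to missing data exists in one arm only. No analysis method recovers assessments that were not made on time.

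**Working it through.** **1. The plan's own figure.** Sample size calculation gives d = 0.25 (f = 0.125), two groups, three measurements, r = 0.60, power 0.80 and alpha 0.05. For the within-between interaction, λ = f²·N·m/(1 − r), with df1 = 2 and df2 = 2(N − 2). At N = 84, λ = 0.015625 × 84 × 3 / 0.40 = 9.84 and power is 0.801; at N = 82 it is 0.791. So 84 reproduces. Then 84 × 1.10 = 92.4, rounded up to 93. With 1:1 allocation that is 93/2 = 46.5, about 46 families per arm.

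**2. The schedule applied to each kind of family.**

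| Family | T1 | T2 and T3 |
|---|---|---|
| CAU, any use of care | 8 weeks after T0 | 6 and 12 months after T1 |
| Training, third session held | 1 week after session three | 6 and 12 months after T1 |
| Training, no third session | no date | no date |

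The abstract's wording does not close the gap. A family that never starts still has no date. If the wording is read as one week after the last session attended, a family whose first and only session falls k weeks after T0 is assessed at k + 1 weeks. That equals the CAU arm's eight weeks only when k = 7, and the article does not say how soon after T0 the training begins.

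**3. How many families.** The article offers two proxies in its Background: 14.2% dropout in the pilot (non-randomised, N = 28) and 26% premature termination in existing programs.
- 46.5 × 0.142 = 6.6, about 7 families
- 46.5 × 0.26 = 12.1, about 12 families

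**4. Possible bias.** Assume that every such family loses T1 to T3, and that these families do worse than completers with the same T0 by δ SD. The training-arm mean then looks better than it is by p × δ.
- δ = 0.5: 0.142 × 0.5 = 0.071 and 0.26 × 0.5 = 0.13, which is 28% and 52% of d = 0.25
- δ = 0.25 to 0.66: 0.04 to 0.09 SD at 14.2%, and 0.07 to 0.17 SD at 26%, or 14% to 69% of d = 0.25

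An alternative illustration assumes that the training has no effect in families who stop. The completer effect then exceeds the intention-to-treat effect by 1/(1 − 0.142) = 1.17 to 1/(1 − 0.26) = 1.35 times. The two illustrations describe different assumptions and should not be added.

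**5. Power.** Ignoring clustering, power is 0.843 at N = 93, 0.813 with 86.4 families left (93 − 6.6) and 0.785 with 80.9 left (93 − 12.1). This loss is modest; one-sided selection matters more.

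**The case against.** A reader might infer that these families are simply lost, and that the intention-to-treat label hides a comparison of completers with all CAU families. The article does not support that. Nowhere does it say that families who stop the training are withdrawn or left unmeasured. Right after giving the length of participation as about 14 months, Procedure says that care at the center may end sooner if families no longer need or want it, which suggests that measurement is meant to outlast care. The Discussion describes reminders and a lighter measurement burden to keep families in. A fallback date may also stand in the full protocol, which is not shown, and an article may leave such detail to it.

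A reader might also infer that the training effect must come out too large. That does not follow either. The Discussion expects disappointed CAU parents to be more likely to leave the study, so the control arm will not be fully observed and the net direction of bias is unknown.

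The dropout rates are weak proxies. The pilot figure does not say whether dropout means leaving the training or leaving the study, and the 26% comes from other programs, typically longer than this one.

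All of this limits the size of the point and how firmly it can be put. It does not remove it. An intention to keep measuring, without a date, leaves the schedule undefined for these families. The article also goes beyond silence: it states an explicit rule for each arm, and one of the rules cannot be applied to part of the randomised population.

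**Conclusion.** The point holds as a defect in the visit schedule. T1 to T3 are undefined for randomised training-arm families without a third session, and this sits badly with the intention-to-treat analysis. About 7 to 12 of about 46 families could be affected if the proxy rates apply. The 0.07 to 0.13 SD figure rests on two assumptions that the article does not supply: complete loss of T1 to T3 in these families, and outcomes 0.5 SD worse than those of completers. Actual loss, and the net direction of bias once CAU dropout is counted, cannot be read from the document.

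The care rules need reconciling as a separate matter. One section ends the bar on CAU at T1 and another at the third session. These differ by a week for completers, and neither end point occurs for families who stop earlier.

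**What to change.** In Procedure, add that training-arm families without a third session are assessed eight weeks after T0, as in the CAU arm, with follow-ups six and twelve months after that assessment. State that stopping the training does not end study measurement, so that calls, questionnaires and record extraction continue.

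Word this as an assessment date only. Study design makes T1 the point from which CAU is allowed, so the fallback date should not by itself decide what care these families may have. The sponsor should reconcile Study design with Procedure on that question; no care rule is proposed here.

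The cost is a sentence or two of text and a few extra call weeks, with existing visits and instruments. Some of these families will decline, so the change reduces the selective loss without removing it.
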